**Fig. 3 Fig3:**
[figure not shown]
HIIT and MICT exercise protocol.** a** Conceptual depiction of exercise intensity prescription relative to peak power output measured in watts for high-intensity interval training (HIIT) and** b** moderate-intensity continuous training (MICT)

#### Intervention Adherence and Scientific Rigor

Exercise intensity adherence will be monitored using two methods: (1) Monitoring of heart rate during exercise and (2) Post-exercise heart rate analysis using custom R Studio [62] code. The code provides minute-by-minute minimum, maximum, and average heart rate and graphs the data with target intensity zone highlighted. This code has been developed into an open access package (https://github.com/[name]/ExerciseHRCode) and application (https://biostats-shinyr.kumc.edu/Neurology_ExerciseHR/).

#### Blood Lactate

Following previous procedures [48, 63], blood lactate will be measured as a surrogate marker of exercise intensity [64] at sessions #2, #5, #8, and #11 via fingerstick and lactate meter.

### Outcome Assessments

Post-intervention, the following assessments will be conducted: PROMIS Fatigue Scale, EQ-5D-5 L, MoCA, 10-meter walk test, 6MWT, TBRS submaximal exercise test, FMD, TCD, and MRI if completed at baseline. Participants will also be asked to complete the 8-item Physical Activity Enjoyment Scale (PACES-8) [65] to evaluate exercise acceptance. Every effort will be made to complete testing within 1 week post-intervention.

### Data Management

Participants will be assigned a unique identifier. Data will be stored in REDCap and on our secure network drive.

### Statistical Analysis

The primary aim of this study is to assess the preliminary efficacy of recumbent-stepper HIIT, compared to MICT, on the change in VO₂_peak_ over the 4-week intervention. We will calculate the mean, standard deviation, and 95% confidence intervals (CI) for VO₂_peak_ at each time point for groups, and the between-group difference post-intervention. We will also calculate the change from baseline to the 4-week assessment for each group. Effect size at 4 weeks will be calculated as the difference in means divided by the pooled standard deviation. Given a planned sample size of *N* = 50 with 1:1 allocation, the precision of our effect estimate will be sufficient for this preliminary efficacy trial. For example, assuming a greater improvement in HIIT (4 mL·kg⁻¹·min⁻¹) compared to MICT (2 mL·kg⁻¹·min⁻¹), and a common standard deviation of 4 mL·kg⁻¹·min⁻¹, the half-width of the 95% CI will be approximately 3.6 mL·kg⁻¹·min⁻¹.

We will fit an Analysis of Covariance (ANCOVA) model with 4-week VO₂_peak_ as the response variable. The model will be adjusted for baseline VO₂_peak_, group, and minimization variable (FMA-LE). As this study is designed to assess preliminary efficacy, we will limit adjustment and not include additional covariates. Similarly, subgroup analyses or interaction models will not be conducted due to risk of overinterpretation. Model diagnostics will be performed using residual plots, and transformations or alternative models if necessary to improve fit. The results from this trial are intended to provide directional estimates and effect size data rather than definitive efficacy, which is critical for designing a fully powered trial.

Additional outcomes, including MCAv, FMD, PWV, 10MWT, 6MWT, and MRI will be assessed in a similar way. Point estimates and 95% CIs will be calculated for the data and model-based estimates will be calculated using an ANCOVA adjusted for the same covariates as the primary outcome. Given the preliminary nature of the study, analyses will be conducted using available data without imputation, with transparent reporting of missingness and attrition.

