**Discussion:**

FAST represents one of the earliest double-blind randomized trials to directly compare HIIT and MICT on a recumbent stepper in people post-stroke, using a validated submaximal exercise testing protocol to individualize exercise intensity. This study will generate preliminary effect sizes for key physiological and functional outcomes obtained with this modality, providing the critical data needed to optimize dosing strategies and power a future definitive trial.

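### The effect size, the trial's stated product, reads as an unadjusted 4-week standardised difference that is not tied to the planned ANCOVA, and its scale is left unclear

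*Protocol article*

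**What the plan says.** In the protocol article, Statistical Analysis, first paragraph, the aim is the effect on change in VO2peak "over the 4-week intervention". The section then lists summaries by group and time point, "and the between-group difference post-intervention", and adds: "We will also calculate the change from baseline to the 4-week assessment for each group". The effect-size definition follows directly: "Effect size at 4 weeks will be calculated as the difference in means divided by the pooled standard deviation". It does not say which means or which SD are meant. The planning example that comes next uses improvements of 4 and 2 mL/kg/min, a common SD of 4 and N = 50, and gives a 95% CI half-width of about 3.6.

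The second paragraph plans an ANCOVA of 4-week VO2peak on group, baseline VO2peak "and minimization variable (FMA-LE"). It does not mention the effect size. The Minimisation section balances allocation on FMA-LE only.

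The role of the effect size is plain. The abstract's Discussion says: "This study will generate preliminary effect sizes for key physiological and functional outcomes obtained with this modality". The Statistical Analysis section says that the results are to give directional estimates and effect-size data "rather than definitive efficacy, which is critical for designing a fully powered trial".

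**The concern.** The figure labelled for use in planning the next trial is not the figure that the trial's own model produces. The only between-group contrast named before the definition is the post-intervention one, and change is described within each group. So the formula reads as raw 4-week means over the pooled 4-week SD.

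Baseline VO2peak is not balanced by design. With 25 per arm, a chance baseline difference feeds into a raw 4-week contrast in proportion to the correlation between the two time points. The ANCOVA removes that component with a covariate that will already have been measured. Leaving it in the headline effect size gives up precision for nothing.

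There is also a question of scale. The aim and the planning example are in terms of change, while the effect size is dated at 4 weeks. A standardised difference on change and one on 4-week values are different numbers for the same treatment effect, and someone planning from the published value must know which one it is.

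**Working it through.** **Inputs from the article.** 25 per arm, assumed difference 2, SD 4 mL/kg/min. The article does not say whether 4 is the SD of VO2peak values or of change.

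**Input assumed.** The correlation r between baseline and 4-week VO2peak, shown from 0.3 to 0.9, with equal SD at both times.

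**The plan's own figure.** Half-width = t(0.975, 48) × 4 × √(2/25) = 2.011 × 1.131 = 2.27, not 3.6. One combination that the article does not state gives 3.60: 4 is the SD of change and r = 0.8, so the 4-week SD is 4/√(2 × 0.2) = 6.32, and the contrast is raw 4-week means (2.011 × 6.32 × 0.2828 = 3.60). This shows that the choice of scale matters. It does not show how the 3.6 was obtained.

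**Reading A: 4 is the SD of VO2peak values.**

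*Baseline imbalance.* SE of the baseline difference = 4 × √(2/25) = 1.13. A difference above 1 in either direction has probability of about 38%, and above 2 about 8%. The raw 4-week difference carries r times the imbalance, so the SD of that error is r × 1.13: 0.57 at r = 0.5 and 0.91 at r = 0.8.

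*Precision of the effect size d (true d = 2/4 = 0.5).*
- Raw: Var ≈ 2/25 + d²/(2 × 50) = 0.0800 + 0.0025 = 0.0825, SE 0.287.
- Adjusted: Var ≈ (1 − r²) × 0.0800 × (1 + 1/46) + 0.0025. The factor 1 + 1/46 is the cost of estimating the baseline slope. FMA-LE is close to balanced by design and adds little.

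I checked this by simulation: 60,000 trials per r, ANCOVA on baseline and a two-level FMA-LE factor with no effect of its own, adjusted difference over the pooled baseline SD.

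| r | Adjusted Var (formula) | Ratio raw/adjusted (formula) | SD raw d (simulated) | SD adjusted d (simulated) | Ratio (simulated) |
|---|---|---|---|---|---|
| 0.3 | 0.0769 | 1.07 | 0.294 | 0.287 | 1.05 |
| 0.5 | 0.0638 | 1.29 | 0.295 | 0.261 | 1.27 |
| 0.7 | 0.0442 | 1.87 | 0.295 | 0.219 | 1.82 |
| 0.8 | 0.0319 | 2.58 | 0.294 | 0.185 | 2.52 |
| 0.9 | 0.0180 | 4.58 | 0.295 | 0.139 | 4.50 |

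Both ratio columns agree within 0.1 with about 1.1, 1.3, 1.9, 2.5 and 4.6. The mean of d was 0.51 for both versions at every r, so neither is biased relative to the other. Dividing by the pooled 4-week SD instead of the baseline SD gave the same adjusted SDs to three decimals.

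**Reading B: 4 is the SD of change.** The SD of values is 4/√(2(1 − r)). The same 2-unit difference is 2/4 = 0.50 on change. On 4-week values it is:
- r = 0.7: 2/5.16 = 0.39
- r = 0.8: 2/6.32 = 0.32
- r = 0.9: 2/8.94 = 0.22

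Readings A and B are alternatives and cannot both apply.

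**The case against.** The other side has several sound points.

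- **The adjusted result is not lost.** The ANCOVA is planned, and model-based estimates are planned for the additional outcomes too. A standardised difference on observed means is a conventional descriptive statistic. This stands, and it limits the point to which number carries the effect-size label.
- **The reading is inferred.** The definition does not name its means. The sentence before it concerns change, and the example after it uses improvements. This also stands, but it supports the request to name the means and the SD.
- **The loss of precision is conditional.** At r = 0.3 or below, adjustment gains almost nothing. A reader might infer that the raw effect size is far less precise whatever the data show, or that it is the noisiest choice available. The article gives no correlation to support the first. The second is not generally true: an unadjusted change-score difference has an SD √(2(1 − r)) times that of the raw 4-week difference, which is 1.18 times at r = 0.3.
- **Imbalance is chance error.** A reader might infer bias, or that imbalance passes into the effect size in full. Neither follows. The estimate is unbiased over randomisation, and only r times the imbalance is carried.
- **Consequences for the next trial.** A reader might infer that this formula would leave the definitive trial underpowered. The article does not commit to sizing that trial on the observed point value, and doing so from any estimate based on 50 people would be hazardous, adjusted or not. How a later trial is sized is outside this plan.

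**Conclusion.** The point holds in a limited form. The article fixes a formula for its declared product, and on the natural reading that formula is an unadjusted 4-week contrast with no link to the planned ANCOVA. The cost is avoidable chance error, with a variance about 1.3 to 2.5 times that of the adjusted version at correlations from 0.5 to 0.8, near 1.1 at 0.3 and about 4.6 at 0.9. These figures rest on an SD of 4 for VO2peak values, equal SDs at both times, 25 completers per arm and a true difference of 2.

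The ambiguity of scale is separate and does not depend on precision. If the SD of 4 refers to change, the reported value could be 0.50 or as low as 0.22 for the same effect over the correlations considered. The section's assurance, "with 1:1 allocation, the precision of our effect estimate will be sufficient for this preliminary efficacy trial", does not settle this, since its half-width does not follow from the stated SD and sample size.

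This should be changed, but it does not threaten the validity of the primary comparison.

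**What to change.** Replace the effect-size sentence with a definition tied to the model: the ANCOVA-adjusted between-group difference divided by a named SD (for example the pooled baseline SD), with its 95% CI. Apply it to VO2peak and to the other outcomes analysed by ANCOVA. Beside it, report the residual SD and the correlation between baseline and 4-week values, so that a reader can convert between scales. Keep the raw 4-week standardised difference as a descriptive figure, labelled as such. State whether the SD of 4 in the planning example is an SD of values or of change.

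The cost is one or two sentences in the analysis section and a few lines of code, with no new data. The Trial Status section gives study completion as December 2025, so the change should be dated and, if still possible, recorded before group results are seen.

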**Methods:**

FAST will enroll 50 individuals with chronic stroke into a double-blind, two-arm, parallel-group preliminary efficacy trial. Participants will be stratified by lower extremity motor function and randomized to HIIT or MICT. Exercise sessions will occur three times per week for four weeks using a total body recumbent stepper. The primary outcome is estimated peak oxygen consumption from the Total Body Recumbent Stepper (TBRS) submaximal exercise test. Secondary outcomes include middle cerebral artery velocity at rest and during exercise, flow-mediated dilation and pulse wave velocity. Tertiary outcomes include walking speed and distance.

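### The stated 95% CI half-width of about 3.6 mL/kg/min does not follow from N = 50 at 1:1 with SD 4; those inputs give about 2.3

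*Protocol article*

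**What the plan says.** The Abstract sets the enrolment target: "FAST will enroll 50 individuals with chronic stroke". The Statistical Analysis section repeats the total as "50 with 1:1 allocation" and concludes that "the precision of our effect estimate will be sufficient for this preliminary efficacy trial".

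It then works an example. The inputs are an improvement of 4 mL/kg/min under HIIT ("assuming a greater improvement in HIIT (4") and 2 mL/kg/min under MICT ("compared to MICT (2"), "and a common standard deviation of 4" mL/kg/min. The result is that "the half-width of the 95% CI will be approximately 3.6" mL/kg/min.

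The same section plans two kinds of comparison: an unadjusted between-group difference after the intervention, and an ANCOVA of 4-week VO2peak on group, baseline VO2peak and FMA-LE. On missing data it says that "analyses will be conducted using available data without imputation". It gives no attrition rate and no pre-post correlation, and it does not say whether the SD of 4 belongs to the change or to the 4-week value.

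**The concern.** The sentence supplies what the textbook two-sample half-width needs (number per arm, common SD, confidence level) and then prints a result those inputs do not give. The gap of about 1.3 mL/kg/min is too large for rounding or for the word approximately, given an assumed difference between arms of 2.

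What is at stake is whether the planning figures can be read. This is the only number in the article that supports N = 50. As printed, the reader cannot tell whether the SD, the number analysed, the contrast or the half-width is the one misreported. The possible readings differ materially: at 25 per arm, a half-width of 3.6 implies an SD of about 6.3 rather than 4, which is a variance about 2.5 times as large ((6.33/4)² = 2.50).

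**Working it through.** **Inputs** (Statistical Analysis section): 25 per arm (50 at 1:1), common SD 4 mL/kg/min, two-sided 95% confidence. The assumed improvements of 4 and 2 fix the difference at 2 but do not enter the half-width.

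**1. Attempt to reproduce the printed figure.**

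SE = SD × √(1/25 + 1/25) = 4 × √(2/25) = 1.131

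- t with 48 df: 2.0106 × 1.131 = **2.27**
- normal: 1.960 × 1.131 = **2.22**
- printed: **3.6**; 3.6 / 2.27 = 1.58, so about 58% wider

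**2. Variants that keep 25 per arm and SD 4.**

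| Variant | Result (mL/kg/min) |
|---|---|
| One-sided (normal) | 1.86 |
| 99% CI (t) | 3.03 |
| Bonferroni for three comparisons | 2.81 |
| Full width rather than half-width | 4.55 |
| One arm's own CI: half-width / full width | 1.65 / 3.30 |
| 4 is the per-visit SD, change analysed, r = 0 | 3.22 |
| Same, r = 0.5 | 2.27 |
| Planned ANCOVA (46 df) | at most 2.28 |

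Here r is the pre-post correlation, which the article does not give. For the per-visit reading, the SD of change is 4 × √(2(1 − r)), which is 5.657 at r = 0. For the ANCOVA, the residual SD is 4 × √(1 − r²) if 4 is the SD of the values and 4 × √((1 + r)/2) if 4 is the SD of change. Neither exceeds 4, which is why 2.28 is the ceiling (2.0129 × 4 × √(2/25)).

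**3. Attrition.** No rate is stated. Assumed losses of 10%, 20%, 30% and 40% at SD 4 give 2.41, 2.56, 2.75 and 2.99.

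**4. What would give 3.6.**

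- *A larger SD at 25 per arm:* 3.6 / (2.0106 × √(2/25)) = 6.33 (6.49 with the normal value).
- *One way that SD could arise:* suppose 4 is the SD of change and r = 0.8 (assumed). The SD at 4 weeks is then 4 / √(2 × 0.2) = 6.32, and the unadjusted 4-week contrast has half-width 2.0106 × 6.32 × √(2/25) = 3.60.
- *Fewer evaluable at SD 4:* 3.56 with 11 per arm, 3.76 with 10 per arm.
- *Per-visit SD 4, change analysed, r = 0, 20 completers per arm:* t(38) × 5.657 × √(2/20) = 3.62.

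Each route needs at least one value that the article does not state.

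**The case against.** The best defence is that 3.6 may rest on an assumption left out of a condensed article, rather than on a slip. The route through a 4-week SD of 6.32 has some force. The SD of 4 directly follows the assumed improvements, so reading it as the SD of change is natural. The post-intervention difference is a contrast the section says it will estimate. The route also needs no attrition. It does not rescue the sentence, because the correlation of 0.8 appears nowhere and nothing shows that the authors used it. It does mean that a reader who infers that 3.6 is unreachable at N = 50 goes too far. It also means that stating the missing assumptions is as good a remedy as changing the number.

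A second tempting inference is that the precision claim itself fails, because an interval around a difference of 2 would include zero at either half-width (−1.6 to 5.6 at 3.6; about −0.3 to 4.3 at 2.27). The document does not support that reading. It never says the interval should exclude zero, and it presents the results as directional estimates and effect-size data for planning a larger trial, not as definitive efficacy.

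Third, the half-widths for the ANCOVA-adjusted difference and for expected completers are details an article may leave to the full protocol or analysis plan, so their absence is no fault here. For the same reason, calling 3.6 the only quantitative support for the sample size is true of this article and may not be true of the full protocol.

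Finally, the figure is offered as an example, and it changes no endpoint, model or allocation. That stands and limits the consequence, but a worked example should still follow from its own inputs.

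**Conclusion.** The concern holds as an arithmetic inconsistency. With 25 per arm, a common SD of 4, no attrition and a two-sided 95% interval, the half-width is about 2.3 mL/kg/min (2.27 by t, 2.22 by normal), not 3.6. The reproduction is exact on the stated inputs; what cannot be settled from the article is which published figure is wrong or which assumption is missing.

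A reader might infer that the trial is too small. The documents do not support that. If SD 4 and N = 50 are right, the error is conservative: the interval would be narrower than printed, and no more participants would be needed. If 3.6 is what was intended, then the SD, the number evaluable, the contrast or the correlation behind it has not been reported.

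**What to change.** Amend the one sentence in the Statistical Analysis section in either of two ways:

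- replace 3.6 with about 2.3 mL/kg/min and state its basis (25 per arm, SD 4, no attrition); or
- keep 3.6 and state what produces it: the SD, the contrast, the pre-post correlation and the completers per arm.

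In both cases, say whether the SD of 4 refers to the change from baseline or to the 4-week value. The authors should choose between the two by going back to their own calculation. The Trial Status section reports study completion in December 2025, so this is a correction of text. It costs one or two sentences, with no extra participants and no change to the design or analysis.

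### As worded, the secondary-outcome ANCOVAs inherit baseline VO2peak as their only baseline covariate; each outcome's own baseline should be named

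*Protocol article*

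**What the plan says.** The Statistical Analysis section of the protocol article first sets out the primary model: "We will fit an Analysis of Covariance (ANCOVA) model with 4-week VO₂_peak_ as the response variable". It then lists the terms: "The model will be adjusted for baseline VO₂_peak_, group, and minimization variable (FMA-LE"). Still on the primary model, it adds that "we will limit adjustment and not include additional covariates".

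The next paragraph turns to the other outcomes. A general sentence comes first: "Additional outcomes, including MCAv, FMD, PWV, 10MWT, 6MWT, and MRI will be assessed in a similar way". A specific one follows: "model-based estimates will be calculated using an ANCOVA adjusted for the same covariates as the primary outcome".

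The section defines the effect size at 4 weeks separately, as the raw mean difference over the pooled SD. Under Trial Design, the outcomes in Table 1 are to be measured both before and after the intervention.

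**The concern.** The primary covariate list names baseline VO2peak specifically, not the baseline value of whatever outcome is being analysed. Carried over unchanged to FMD or the 6-minute walk, it adjusts the 4-week value for baseline fitness and leaves out baseline FMD or baseline walking distance. An outcome's own baseline is usually its strongest predictor, and the hypotheses are about improvement. A model without it estimates the between-group difference less efficiently.

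Two things are at stake. The first is the precision of every secondary and additional model-based estimate in a trial of 50. The second is discretion: two competent analysts could fit different models and each cite this section. Minimisation is on FMA-LE alone, so the design does not directly balance MCAv, FMD, PWV or walking at baseline.

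**Working it through.** **The plan's own figure.** The section gives no precision figure for any secondary outcome, so there is none to reproduce. Its one figure, a 95% CI half-width of about 3.6 mL/kg/min, is for VO2peak. The stated inputs ("Given a planned sample size of *N* = 50 with 1:1 allocation" and "a common standard deviation of 4 mL·kg⁻¹·min⁻¹") give t(0.975, 48) × 4 × √(2/25) = 2.011 × 4 × 0.283 = 2.27. That mismatch is a separate matter and does not enter this point.

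**Step 1: the two readings.**
- Literal: 4-week outcome on group, baseline VO2peak and FMA-LE.
- Analogous: 4-week outcome on group, own baseline and FMA-LE.

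The general sentence favours the second reading and the specific sentence favours the first. Nothing else in the article decides between them.

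**Step 2: loss of precision under the literal reading.** Inputs:
- ρ is the correlation of an outcome's own baseline with its 4-week value.
- r_V is the correlation of baseline VO2peak with that 4-week value.
- Both are assumptions, since the article gives neither. FMA-LE is in both models.

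ANCOVA residual variance is proportional to one minus the squared correlation, so:

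- variance ratio (literal over analogous) = (1 − r_V²)/(1 − ρ²)
- CI-width ratio = square root of the variance ratio
- effective sample size = 50 / variance ratio

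| ρ | r_V | Variance ratio | CI-width ratio | 50 participants are worth |
|---|---|---|---|---|
| 0.5 | 0 | 1/0.75 = 1.33 | 1.15 | 38 |
| 0.5 | 0.3 | 0.91/0.75 = 1.21 | 1.10 | 41 |
| 0.7 | 0 | 1/0.51 = 1.96 | 1.40 | 26 |
| 0.7 | 0.5 | 0.75/0.51 = 1.47 | 1.21 | 34 |
| 0.8 | 0 | 1/0.36 = 2.78 | 1.67 | 18 |
| 0.8 | 0.5 | 0.75/0.36 = 2.08 | 1.44 | 24 |

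The rows with r_V = 0 are upper bounds, because there baseline VO2peak explains nothing.

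**Step 3: chance imbalance.** With 25 per arm, the baseline difference between arms has a standard error of √(2/25) = 0.28 outcome SDs. If r_0 is the correlation between baseline VO2peak and the outcome's own baseline, the literal model passes on ρ − r_V × r_0 SDs per SD of imbalance:

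- ρ 0.6, r_0 0.4, r_V 0.24: 0.6 − 0.096 = 0.50
- ρ 0.8, r_0 0.4, r_V 0.32: 0.8 − 0.128 = 0.67
- ρ 0.9, r_0 0.6, r_V 0.54: 0.9 − 0.324 = 0.58

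**Step 4: check by simulation** (25 per arm, no true effect, 8,000 runs per scenario, FMA-LE simulated as unrelated to the outcome). In the same three scenarios:

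- The CI-width penalty was 1.21, 1.56 and 1.95, against 1.21, 1.58 and 1.93 from the formula.
- The carry-over slopes were 0.51, 0.66 and 0.58 for the literal model and about 0 for the own-baseline model.
- The mean estimate over all runs was about 0 for both models.

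A one-standard-error imbalance would therefore move the literal estimate by about 0.51 × 0.28 = 0.14 to 0.66 × 0.28 = 0.19 SDs.

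**The case against.** The strongest reply is that the general sentence governs. The primary model adjusts a 4-week outcome for its own baseline, group and the minimisation variable. To treat FMD in like manner is to adjust 4-week FMD for baseline FMD, and the covariates are then the same in role. Nowhere does the article say that baseline VO2peak replaces an outcome's own baseline. It is also a condensed article, and a covariate list for each outcome is commonly left to the full protocol or SAP.

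Much of this stands. The own-baseline model is a plausible intent, so a reader who infers that the investigators have decided against own baselines goes further than the text allows. But the article did not leave the secondary covariates to another document. It specified them, in words that point to the wrong baseline.

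A reader might also infer that own baselines are forbidden, because additional covariates are excluded. That exclusion is stated for the primary model, and under the analogous reading an own baseline is not an additional covariate.

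Nor does Table 1 settle the matter by describing MCAv as a change. It describes the primary outcome as a change too, yet that outcome is modelled as a 4-week value with its own baseline as covariate.

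**Conclusion.** The point holds as a wording defect with a real statistical consequence under one of two available readings. The rule followed word for word omits each secondary and additional outcome's own baseline. The 95% CI is then about 1.10 to 1.15 times as wide at an own-baseline correlation of 0.5, 1.21 to 1.40 times at 0.7, and 1.44 to 1.67 times at 0.8. These figures rest wholly on assumed correlations. Under the analogous reading there is no loss.

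Two stronger conclusions are not supported. One is that the literal model is biased. Averaged over randomisations it is not; the cost is lower precision and a conditional error in the one sample observed. The other is that the trial's standardised effect sizes would be distorted by this choice. The section defines them from raw 4-week means and the pooled SD, so the ANCOVA covariates do not alter them. Only the model-based secondary and additional estimates are touched, and the primary analysis is unaffected.

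**What to change.** Replace the covariate sentence with: each outcome's 4-week value will be analysed by ANCOVA with group, the baseline value of that same outcome, and FMA-LE; baseline VO2peak enters only the primary model.

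The change costs one sentence and needs no new data, since the Table 1 outcomes are already measured before the intervention. MRI is repeated only in those who had it at baseline, so no post-intervention scan lacks a baseline scan. The one small price is that, with available data and no imputation, a participant without a baseline value for some other outcome drops out of that outcome's model.

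Trial Status gives study completion as December 2025, so the wording should be settled before these outcomes are compared by group. If that comparison has already been made, the report should say which model was used and when it was chosen.
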